### Randomization

The participants of control and intervention groups were assigned randomly at a ratio 1:1.

#### Sequence generation

The method of assigning participants to study groups was performed in the form of block randomization (with random blocks of 4 alleles and with a size of 8), which was performed by the specialized random allocation software.

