### Sample size

The sample size estimation of the main RCT was based on data from the ASPRE trial (6). The results of this trial showed that preterm PE occurred in 1.6% of the intervention group as compared with 4.3% in the placebo group. We calculated that the enrollment of 1792 participants in a 1:1 ratio of distribution (896 participants in each group) would provide the trial with a power of 90% (alpha level of 5%). If we are allowed a 10% loss to follow-up, the sample size will reach 986 participants in each group. A total of 1972 eligible participants will be randomly selected to participate in the trial arms. Furthermore, we proposed a sample size of 200 high-risk pregnancies in the pilot study and quality control. By screening 1686 pregnant women who attended the Maternal-Fetal hospital Clinic, we achieved this sample size. From January 2023, after obtaining written conscious consent, the trial began with 100 participants in each group at a 1:1 ratio, randomly.

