#### Allocation mechanism

Due to the non-blindness of the trial, concealment was not performed.

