#### Implementation

The perinatology fellowship assistant randomly did the allocation. The registration of participants was done by the personnel of the Prenatal Clinic of Vali-E-Asr hospital.

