### Blinding

Due to the nature of the intervention, neither participants nor researchers could be blinded to allocation. However, assessments will be conducted by a blind analyzer for trial allocation.

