#### Accessibility of data

This script constitutes the complete protocol. Following the completion of the study information used in this study will be obtained from the corresponding author upon rational request.

**Table 2 T2:** Data collection form

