### Strengths and limitations of the trial

1. This is the large single-center RCT to compare the effect of aspirin administration from early pregnancy versus after 11 wk in women at risk of PE.

2. Screening and start of prevention with aspirin from the early stage of pregnancy in high-risk women can provide an opportunity for more effective prevention of PE.

3. Follow-up of newborns is only confined to the primary postnatal period for the time of stay in the hospital.

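### The block rule is unclear but short on every reading and is published for an open, single-centre trial, so upcoming assignments can often be guessed even if the list were concealed

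*Protocol article*

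**What the plan says.** All of this is in the protocol article.

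- **Sequence generation:** block randomisation by dedicated software, "with random blocks of 4 alleles and with a size of 8". The section does not say whether 4 and 8 are two block lengths, or whether 4 is the number per arm in a block of 8. It does not separate the pilot list from the main-trial list.
- **Randomization:** the ratio is 1:1, and no stratification is mentioned.
- **Allocation mechanism:** "Due to the non-blindness of the trial, concealment was not performed".
- **Implementation:** "The perinatology fellowship assistant randomly did the allocation", while clinic personnel register the women.
- **Blinding:** "neither participants nor researchers could be blinded to allocation".
- **Strengths and limitations of the trial:** "This is the large single-center RCT".
- **Accessibility of data:** "This script constitutes the complete protocol". The block rule is therefore public.
- **Sample size and Trial status:** 1972 women are planned for the main trial, and its recruitment began in October 2023.

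**The concern.** Permuted blocks force balance every few women. Anyone who sees the assignments in order and knows the block length can count what is left in the current block. Three conditions make this easy here: assignments are open, one centre apparently runs one sequence, and the block rule is published. Hiding the list does not remove the problem, because the pattern can be inferred from assignments already seen.

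Staff who expect a given arm next can enrol, postpone or decline a woman according to how risky she looks. Some eligibility items leave room for judgement: low socioeconomic level, other adverse pregnancy outcomes, and a significant haematoma have no stated threshold. The arms would then differ at baseline in ways that randomisation is meant to exclude. The planned logistic regression adjusts only for background variables found to differ between the groups, so it cannot remove selection on risk that nobody recorded.

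**Working it through.** The protocol gives no predictability figure to reproduce. The inputs taken from it are the block sizes 4 and 8, the 1:1 ratio, open assignments, one centre and 1972 women. Two assumptions are added: the observer has tracked every earlier assignment, and in the mixed case lengths 4 and 8 are equally likely.

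**1. Assignments known for certain, fixed block of 2m.** An assignment is forced once one arm's quota in the block is used up. Averaged over all balanced blocks, the forced share is 1/(m+1).
- Block of 4 (m = 2): 1/3 = 33.3%.
- Block of 8 (m = 4): 1/5 = 20.0%.

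**2. Correct guesses, fixed block.** The observer always guesses the arm with more places left and tosses a coin at ties. Expected correct guesses per block are m + 2^(2m-1)/C(2m,m) - 1/2.
- Block of 4: 2 + 8/6 - 0.5 = 2.833; divided by 4 = 70.8%.
- Block of 8: 4 + 128/70 - 0.5 = 5.329; divided by 8 = 66.6%.

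Full enumeration of all balanced blocks gives the same values.

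**3. Random mix of 4 and 8.** This was simulated with 200 sequences of 1972. The observer knows the two possible lengths but not the block boundaries, and keeps track of every block state consistent with what has been seen.

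| Reading of the block rule | Known for certain | Guessed correctly (p) | 2p - 1 |
|---|---|---|---|
| Fixed 4 | 33.3% | 70.8% | 0.42 |
| Fixed 8 (including 4 per arm) | 20.0% | 66.6% | 0.33 |
| Random mix of 4 and 8 | 7.7% | 68.0% | 0.36 |
| Simple randomisation | 0% | 50% | 0 |

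In the mixed case, about 24.5% would be certain if the boundaries were also known.

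**4. From guessing to bias.** Let d be the difference in pre-eclampsia risk between women enrolled when early aspirin is expected and women enrolled when control is expected. A share p of the early arm, and 1 - p of the control arm, was enrolled under the first expectation. The spurious difference between arms is d x [p - (1 - p)] = d(2p - 1), that is 0.33d to 0.42d. It depends on guessing success, not on certainty, so the mixed reading falls inside the range.

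The documents give no value for d. For illustration only:
- d = 0.5 points: 0.17 to 0.21 points.
- d = 1 point: 0.33 to 0.42 points.
- d = 2 points: 0.67 to 0.83 points.

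The difference used for the sample size is 4.3 - 1.6 = 2.7 points. To produce that much by steering alone, d would have to be 2.7/0.417 = 6.5 to 2.7/0.332 = 8.1 points.

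**5. What longer blocks would achieve.** The formulas in steps 1 and 2 give 14.3% certain and 64.3% guessed for a fixed block of 12, and 11.1% and 62.8% for a fixed block of 16. An equal random mix of 8, 12 and 16, simulated as in step 3 with 100 sequences, gives about 1.7% certain and 64% guessed, even if the observer knew the possible lengths.

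**The case against.** **The certainty figure depends on the reading.** A reader might infer that staff can deduce 20-33% of assignments whatever the rule means. The text does not support that. The quoted phrase contains the word random, so varied lengths are a fair reading, and the certain share then drops to about 8%. This objection stands. Guessing success of 67-71% is what holds on every reading.

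**The two numbers need not conflict.** It is tempting to call 4 and 8 a contradiction. Four per arm in blocks of 8, or lengths varied between 4 and 8, would each be consistent. What is shown is unclear wording.

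**Concealment is the larger problem.** With no concealment, the next assignment may simply be known, and counting blocks adds little. This stands as a matter of priority. The block rule becomes a separate problem once the list is hidden, and then it limits what hiding the list can achieve.

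**Tracking is assumed.** The Blinding section says that allocation is open, not that recruiting staff follow the ordered sequence, and allocation and registration are done by different people. The percentages are therefore what a fully informed observer could reach, not a record of what happened.

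**The bias has no documented size.** Setting a 2-point d beside the 2.7-point planning difference could suggest a known distortion. No value of d has a source in the documents. The 2.7 points come from preterm pre-eclampsia under aspirin against placebo, whereas here both arms receive aspirin and the primary outcome covers early and late onset. The comparison gives scale only.

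**Conclusion.** The point holds in a conditional form. The block rule cannot be read with certainty, but every reading gives short blocks, and the rule is public in an open, single-centre trial without concealment. An observer who tracked all earlier assignments, even with the list hidden, would know 33%, 20% or about 8% of assignments for certain (fixed 4, fixed 8, random mix). The same observer would guess 67-71% correctly in every case, against 50% without predictability. If enrolment followed those guesses, the bias would be 0.33d to 0.42d, with d unknown and its direction open.

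The documents do not show that anyone steered enrolment, and no such inference should be drawn. The design leaves the route open, and the planned analysis could not reliably repair the result. A correction is worthwhile because it is cheap and recruitment to the main trial had only recently begun when the article was written.

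**What to change.** 1. State in one unambiguous sentence the block scheme used so far, separately for the pilot and the main trial if they differ.
2. For women still to be enrolled, use a new list that is concealed and held by someone not involved in recruitment, with each assignment released only after a woman is irrevocably enrolled. Without this step a new list gains nothing.
3. Generate that list with longer, randomly mixed block lengths that are withheld from recruiting staff and reported only after the trial ends, or use simple randomisation. Longer mixed blocks nearly remove certain assignments (about 1.7% for a mix of 8, 12 and 16) but still allow about 64% correct guesses if the lengths became known. Of these options, only simple randomisation removes predictability altogether.

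The cost is a new list, a custodian for it and a short protocol change. With blocks, the arm-size difference is at most half the longest block, for example 8 women for a longest block of 16. If all 1972 were randomised simply, the standard deviation of the difference would be the square root of 1972, about 44. A difference of 88 (1030 against 942), about two standard deviations, has the precision of 2 x 1030 x 942/1972 = 984 women per arm instead of 986, which is negligible for power.

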#### Allocation mechanism

Due to the non-blindness of the trial, concealment was not performed.

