### Ethical considerations

The trial was verified by the ethics committee of the Tehran University of Medical Sciences, Tehran, Iran Institutional Review board (Code: IR.TUMS.IKHC.REC.1401.215) on October 18, 2022, and steered conforming to the Declaration of Helsinki and later reconsiderations.

Written informed consent was acquired from all participants by the interviewer who included perinatology fellowship or prenatal clinic treatment staff. Participants are informed that their participation is voluntary and they may withdraw from the trial at any time without negative consequences on their treatment. The trial was registered on January 7, 2023, at the Iranian Registry of Clinical Trial (http://www.irctir/; IRCT ID: IRCT20221126056611N1). The last registry update was confirmed on 2023–12-21.

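### Allocation was left unconcealed on the ground that the trial is open-label; that ground is invalid, and nothing stated stops recruiting staff from foreseeing the next assignment

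*Protocol article*

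**What the plan says.** The Allocation mechanism section of the protocol article is a single sentence: "Due to the non-blindness of the trial, concealment was not performed".

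The neighbouring sections fill in the setting:

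- **Sequence generation:** a software-generated block sequence, described as "with random blocks of 4 alleles and with a size of 8".
- **Implementation:** "The perinatology fellowship assistant randomly did the allocation", and "The registration of participants was done by the personnel of the Prenatal Clinic of Vali-E-Asr hospital".
- **Ethical considerations:** "Written informed consent was acquired from all participants by the interviewer who included perinatology fellowship or prenatal clinic treatment staff".
- **Blinding:** "neither participants nor researchers could be blinded to allocation". Only the assessment or analysis is blind.
- **Strengths and limitations:** the trial has a single centre.

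No sealed envelopes, central or web release, or independent holder of the list is mentioned. No separate mechanism is given for the main trial.

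**The concern.** The stated reason confuses two safeguards. Blinding concerns what is known after assignment. Concealment hides the coming assignment until the woman has been found eligible, has consented and is registered. An open-label trial can have full concealment, and needs it more than a blinded trial does, because past assignments are visible and help to predict the next one.

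Without concealment, the decision to enrol an eligible woman, to defer her or not to invite her can depend on the arm that comes next. The design gives staff a practical motive. The exclusion criteria admit women up to 16 wk, while the Intervention section defines the intervention arm by aspirin started before 11 wk. Gestational age at presentation is therefore an obvious reason to match women to arms. Some entry criteria also leave room for judgement, such as low socioeconomic level, other adverse obstetric history, or whether a haematoma is significant.

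At stake is the comparability of the arms for the primary outcome, which randomisation is meant to secure.

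**Working it through.** **1. Does any other section supply concealment?**

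| Section | What it provides | Does it hide the next assignment? |
|---|---|---|
| Sequence generation | Random blocks from software | No. This gives an unpredictable list, not a hidden one |
| Implementation | One person allocates, others register | Not as described. No rule says that release follows registration |
| Ethical considerations | Fellowship or clinic staff take consent | No. Consent comes from the same two staff groups that allocate and register |
| Blinding | Blind analyser | No. It acts after enrolment |
| Statistical analysis | Logistic regression adjusted for background variables that differ between arms | No. It reaches only measured variables |

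**2. How predictable is a block when past assignments are known?** Assumptions: the list itself is hidden, past assignments are known, and one fixed block size 2m is used and known. The article does not establish the last of these.

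- Fraction of assignments known with certainty: 1/(m + 1).
  - Size 4 (m = 2): 1/3 = 33.3%. Check by listing the 6 possible sequences: two of them (AABB, BBAA) leave 2 certain assignments and the other four leave 1. That is (2×2 + 4×1)/6 = 1.33 per block, and 1.33/4 = 33.3%.
  - Size 8 (m = 4): 1/5 = 20.0%.
- Fraction guessed correctly by always naming the arm with more places left: [m + 2^(2m−1)/C(2m, m) − 0.5]/(2m).
  - Size 4: (2 + 8/6 − 0.5)/4 = 2.833/4 = 70.8%.
  - Size 8: (4 + 128/70 − 0.5)/8 = 5.329/8 = 66.6%.
- With no information the figure is 50%. If the list itself were in view, it would be 100%.

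Exact enumeration of both block sizes gave the same values.

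**3. What could selection do to the test?** This step is purely illustrative. Inputs from the Sample size section: 4.3% versus 1.6%, 90% power, alpha 5%, 896 per arm. The stated size reproduces. The two-sided two-proportion formula gives 824 per arm without continuity correction and 896 with it. The concern does not affect this figure.

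Now assume no treatment effect, a 4.3% risk in one arm, and a baseline risk lowered in the other arm by selection alone. With p1 = 0.043, p2 = 0.043 × r, d = p1 − p2, and p̄ the mean of p1 and p2:

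- SE0 = √[2p̄(1 − p̄)/896]
- SE1 = √[(p1(1 − p1) + p2(1 − p2))/896]
- Rejection probability = Φ[(d − 1.96·SE0)/SE1] + Φ[(−d − 1.96·SE0)/SE1]

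For r = 0.9: p2 = 0.0387, d = 0.0043, and both standard errors are 0.00935. The result is Φ(−1.50) + Φ(−2.42) = 0.067 + 0.008 = 0.075.

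| Baseline risk lower in one arm by | Two-sided false-positive rate |
|---|---|
| 0% | 5.0% |
| 10% | 7.5% |
| 20% | 15.7% |
| 30% | 30.7% |

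The risk shifts are assumptions. The 4.3% is the placebo rate of preterm pre-eclampsia used in the plan's sample size, not a forecast for this trial. The table shows only that, with rare events, a modest imbalance at entry can look like an effect.

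**The case against.** The best defence is that the allocator and the registrar are different people, that the sequence is random, and that the past tense may describe only the pilot. Part of this stands. The split of tasks is real and should be acknowledged. It is weak, however, because consent is taken by the same two groups and no rule ties release of the assignment to completed registration. The past tense leaves the scope open, but the section describes the trial in general and no other mechanism is given for the main trial. Nor is this detail that an article leaves to a fuller document: the sentence affirms that concealment was absent, and the article describes itself as the complete protocol.

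Several stronger readings are tempting and are not supported:

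- *The list was open to recruiters, so every assignment was foreseeable.* The article reports no concealment step. It does not say that recruiters held or saw the list. The 100% figure applies only if they did.
- *The protocol claims that concealment is impossible without blinding.* It says that concealment was not done, and gives non-blindness as the reason.
- *The block figures describe this trial.* "with random blocks of 4 alleles and with a size of 8" may mean a fixed size or sizes varied between 4 and 8. If they vary, the figures do not apply exactly. Nothing says that recruiters knew the sizes.
- *Women with recent bleeding could be steered between arms.* Vaginal bleeding excludes a woman from both arms, so it is a poor example.
- *Selection took place.* No section reports that.

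**Conclusion.** The concern holds as a defect in what the protocol states: an invalid reason is given for omitting concealment, and no stated safeguard takes its place. Carried out as written, a single-centre open trial is exposed to selection at entry that later analysis cannot reliably remove. This must be fixed, because it bears on the validity of the primary comparison.

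The size of any bias cannot be derived from the article. Predictability of 71% (size 4) or 67% (size 8), with 33% or 20% of assignments certain, rests on fixed and known block sizes and known past assignments. The false-positive rates of 7.5% to 30.7% rest on assumed shifts in baseline risk. Both are illustrations. The conclusion itself rests on no figure.

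**What to change.** 1. For all remaining main-trial allocations, have someone independent of recruitment hold the sequence. Release each assignment by central phone or web, or by sequentially numbered opaque sealed envelopes, only after eligibility, consent and registration are logged.
2. Do not disclose block sizes to recruiters. Since the article names 4 and 8, a fresh scheme for the remaining allocations is sensible. State clearly whether the existing sizes were fixed or varied.
3. Replace the rationale in the Allocation mechanism section. It should no longer give lack of blinding as the reason for omitting concealment.
4. Report the allocations made without concealment as a limitation, with their number, and add a sensitivity analysis of the primary outcome before and after concealment began.
5. If the main trial already conceals allocation and the sentence describes only the pilot, say so and describe the method.

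The cost is small: envelopes or a web tool, and a short amendment. Women already randomised stay in their assigned arms. The main trial plans 1972 women and began recruiting in October 2023. The article does not say how many allocations remain, so how much the change can still protect is unknown.

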#### Implementation

The perinatology fellowship assistant randomly did the allocation. The registration of participants was done by the personnel of the Prenatal Clinic of Vali-E-Asr hospital.

### Blinding

Due to the nature of the intervention, neither participants nor researchers could be blinded to allocation. However, assessments will be conducted by a blind analyzer for trial allocation.

### Intervention

After the participant screening, written informed consent was obtained from them, which was approved by the Tehran University Ethics Committee, Tehran, Iran.

During the first visit, vital signs, including blood pressure, weight, and height for accounting for body mass index, were measured. A complete record of medication usage is obtained, particularly those that interact with aspirin, such as anticoagulants, antiplatelet agents such as clopidogrel, antidepressants, and corticosteroids, smoking, and alcohol consumption. 30 days after aspirin was administered, a follow-up telephone interview was conducted for side effects and adverse events. At each clinical visit, PE symptoms and the presence of edema were noted and recorded. In addition, participants were asked about the possible side effects of aspirin.

In the pilot study, 200 eligible participants were randomly selected (100 participants in each group). Individuals who received LDA before 11 wk of gestation (optimally from the detection of the fetal heartbeat by ultrasound exam) were considered the intervention group and those who receive LDA after 11 wk are the control group. In the control group, the cut-off gestational age to prescribe aspirin was 16 wk. In both groups, the initial dose of aspirin is 80 mg per day, and it will be continued until 36 wk or in the case of premature delivery.

The mean UtA-PI is measured simultaneously with nuchal translucency (NT) determined through a transabdominal ultrasound exam at 11–13
${\;}^{6/7}$
 wk. In addition, a combined aneuploidy screening test was requested by measuring the maternal serum-free beta-human chorionic gonadotropin (β-hCG) and pregnancy-associated plasma protein-A (PAPP-A) using the Cobas-E-411 analyzer.

If there are any criteria, the initial dose of aspirin (80 mg) is changed to 150 mg per day:

•
 PAPP-A 
<
 0.4 in the first trimester (15)

•
 PE risk greater than or equal to 1/100 in the aneuploidy screening test (16)

•
 High resistance of uterine arteries in color Doppler ultrasound (the mean UTA-PI 
>
 95
${\;}^{\text{th}}$
 percentile or bilateral notching) (17)

At 18–22 wk, the mean UtA-PI will be measured and recorded at the same time as the anomaly scan. Ultrasound examinations are performed by 2 trained prenatal fellowships that have Fetal Medicine Foundation certification.

During the trial, some participants may be excluded from the study due to reasons such as abortion or IUFD below 20 wk of gestation or major fetal abnormalities or side effects of aspirin or discontinue the intervention. We will use the CONSORT checklist when writing our report.

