#### Exclusion criteria

1) Hypersensitivity to nonsteroidal anti-inflammatory drug products

2) Asthma, rhinitis, and nasal polyps

3) Severe renal or severe hepatic impairment

4) History of gastrointestinal bleeding or active peptic ulcer disease

5) Vaginal bleeding or significant hematoma on ultrasound

6) Gestational age 
>
 16 wk

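### Entry is open to 16 wk but the intervention must start before 11 wk, so some eligible women can be randomised to an arm already closed to them; groups are also worded by receipt of aspirin

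*Protocol article*

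**What the plan says.** **Entry.** The last item under Exclusion criteria, "6) Gestational age", removes women above 16 wk. The Inclusion criteria list risk factors and add no gestational-age limit.

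**Arms.** The Intervention section describes the early arm as "Individuals who received LDA before 11 wk of gestation (optimally from the detection of the fetal heartbeat by ultrasound exam") and continues that these women "were considered the intervention group and those who receive LDA after 11 wk are the control group". It then adds: "In the control group, the cut-off gestational age to prescribe aspirin was 16 wk".

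**Allocation.** Under Randomization: "The participants of control and intervention groups were assigned randomly at a ratio 1:1". Sequence generation describes software-generated blocks. For the pilot, the Sample size section says "the trial began with 100 participants in each group at a 1:1 ratio, randomly". Under Allocation mechanism: "Due to the non-blindness of the trial, concealment was not performed".

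**Planning rates.** The sample size rests on an earlier placebo-controlled trial in which "preterm PE occurred in 1.6% of the intervention group as compared with 4.3% in the placebo group". This leads to 896 per group for 90% power at a 5% alpha level, and 986 per group after a 10% allowance for loss to follow-up.

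**The concern.** The trial's question is whether aspirin started before 11 wk prevents more pre-eclampsia than aspirin started later. A randomised answer needs both arms to be open to every woman at the moment she is randomised. The entry window and the intervention window do not give that: between 11 and 16 wk a woman meets the entry rules but can only receive the control timing.

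The arm definition makes this harder to resolve. It classifies women by when they took aspirin, not by the arm they were assigned to. Two readings follow.

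- **Analysed as assigned.** Late entrants assigned to early aspirin actually get control timing. The arms stay comparable, but the contrast shrinks and power falls.
- **Analysed as received.** Late entrants, and early-arm women who start late, join the control group. Gestational age at presentation then decides the group for part of the sample, and the comparison is no longer randomised.

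Unconcealed allocation adds to the worry, because the stated procedure has no safeguard against gestational age at presentation steering assignment.

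**Working it through.** **1. The windows side by side**

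| Gestational age at entry | Eligible? | Early arm possible? | Control arm possible? |
|---|---|---|---|
| below 11 wk | yes | yes | yes |
| 11 to 16 wk | yes | no | yes |
| above 16 wk | no | – | – |

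The middle row is the defect. Nothing in the text restricts randomisation to the first row or says how a woman in the second row is handled. A start at exactly 11 wk fits neither arm as worded (before versus after 11 wk).

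**2. The plan's own figure**

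Inputs from the Sample size section: p1 = 0.016, p2 = 0.043, alpha 5% (taken as two-sided), power 90%, ratio 1:1. With d = 0.027 and mean rate 0.0295:

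- n' = [1.96·√(2·0.0295·0.9705) + 1.2816·√(0.016·0.984 + 0.043·0.957)]² / 0.027² = 823.2, so 824 per arm.
- With continuity correction: n = (n'/4)·[1 + √(1 + 4/(n'·d))]² = 895.8, so **896 per arm**. The stated figure is reproduced.
- 896 × 1.10 = 985.6, the stated 986.

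**3. Analysed as assigned (illustration)**

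Let f be the share of women randomised at 11 to 16 wk. The document does not give f, so 10%, 20% and 30% are assumed. Assume also that late entrants in the early arm have the control risk and that late entry does not itself change risk. Then:

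- Early-arm risk: p1(f) = 0.016·(1 − f) + 0.043·f
- Power = Φ{[(0.043 − p1(f) − c)·√896 − 1.96·√(2·p̄·(1 − p̄))] / √[p1(f)·(1 − p1(f)) + 0.043·0.957]}, where p̄ is the mean of the two rates and c = 1/896 with the continuity correction or 0 without it.

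| f | Early-arm risk | Power, corrected | Power, uncorrected | n per arm for 90%, corrected |
|---|---|---|---|---|
| 0 | 0.0160 | 90% | 92% | 896 |
| 10% | 0.0187 | 81% | 85% | 1143 |
| 20% | 0.0214 | 69% | 74% | 1493 |
| 30% | 0.0241 | 55% | 60% | 2010 |

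The corrected column is the one consistent with the plan's 896.

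**4. Analysed as received (illustration)**

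If all late entrants count as controls, the early group is half of the remaining (1 − f). With 1972 women and f = 20%:

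- early group = 1972 × 0.8 / 2 = 789; control group = 1972 − 789 = 1183;
- late entrants are 0.2 / 0.6 = 33% of controls.

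At f = 30% the late share of controls is 0.3 / 0.65 = 46%. With no true effect, and late presenters assumed to carry 0.8 to 1.5 times the risk of early presenters, the apparent risk ratio is 1 / (0.54 + 0.46 × 0.8) = 1.10 at one end and 1 / (0.54 + 0.46 × 1.5) = 0.81 at the other. The bias can go either way.

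**The case against.** **The receipt wording may be loose drafting.** The article describes 1:1 random assignment in several places, and the sentence defining the groups directly follows one about randomly forming two pilot groups of 100. It can be read as saying what each randomised arm receives. This stands: a reader might infer that late presenters, or early-arm women who started late, were in fact moved to control, but no passage says so and equal pilot groups do not show it. The eligibility conflict remains even if every woman was properly randomised.

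**The sentence concerns the pilot.** It follows a pilot sentence, but it is the only definition of the arms, and the Introduction and Discussion use the same contrast for the whole trial.

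**A survivor bias favouring control.** A reader might infer this because late presenters have already passed the period of early losses. The documents do not support that direction. Pre-eclampsia is defined as developing after 20 wk, so an early loss kept in the early arm's denominator would lower that arm's incidence. The Intervention and Monitoring sections also say that women with losses below 20 wk may be excluded.

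**The power figures borrow a contrast.** This also stands. The 4.3% is a placebo rate, while controls here take aspirin, and nothing in the text shows that f is above zero. The figures show how dilution works; they are not this trial's power.

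**An entry limit may appear in Figure 1.** The flowchart was not visible in the text reviewed, so this cannot be ruled out. A limit given only there would still have to be reconciled with the listed criteria.

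**Conclusion.** The point holds as a conflict within the plan. The entry criteria admit women up to 16 wk, the intervention requires a start before 11 wk, and randomisation is not restricted to women for whom both arms are possible. The wording of the groups by receipt is ambiguous against the stated random assignment; it is not evidence that women were reclassified.

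Followed as written, the plan gives either a diluted contrast or a comparison that is not randomised. The amount depends on an unstated share of late entrants. Under the plan's borrowed rates, each further 10% of late entry costs roughly 9 to 14 percentage points of power (90% to 81%, 69%, 55%). Because the trial asks only about timing around 11 wk, this should be settled before more women are randomised.

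**What to change.** - Reconcile the Inclusion criteria, Exclusion criteria and Intervention sections so that randomisation is limited to women still below the plan's own 11 wk limit for the intervention arm. Keep 16 wk only as the plan's stated limit for starting in the control arm.
- Define both groups by random assignment and analyse them that way. Report the actual gestational age at aspirin start as adherence to the assigned timing.
- Word the boundary so that a start at exactly 11 wk is covered.
- Identify and report, by assigned arm, any women already randomised at or after 11 wk.

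**Cost:** one eligibility amendment and one wording change. Late presenters would no longer be recruited, so enrolment may be somewhat slower; these women cannot inform the early-versus-late question.
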